## Abstract

**Background:**

Self-monitoring of hypertension is associated with lower systolic blood pressure (SBP). However, evidence for the use of self-monitoring to titrate antihypertensive medication by physicians is equivocal. Furthermore, there is some evidence for the efficacy of telemonitoring in the management of hypertension but it is not clear what this adds over and above self-monitoring. This trial aims to evaluate whether GP led antihypertensive titration using self-monitoring results in lower SBP compared to usual care and whether telemonitoring adds anything to self-monitoring alone.

**Methods/Design:**

This will be a pragmatic primary care based, unblinded, randomised controlled trial of self-monitoring of BP with or without telemonitoring compared to usual care. Eligible patients will have poorly controlled hypertension (>140/90 mmHg) and will be recruited from primary care. Participants will be individually randomised to either usual care, self-monitoring alone, or self-monitoring with telemonitoring. The primary outcome of the trial will be difference in clinic SBP between intervention and control groups at 12 months adjusted for baseline SBP, gender, BP target and practice. At least 1110 patients will be sufficient to detect a difference in SBP between self-monitoring with or without telemonitoring and usual care of 5 mmHg with 90% power with an adjusted alpha of 0.017 (2-sided) to adjust for all three pairwise comparisons. Other outcomes will include adherence of anti-hypertensive medication, lifestyle behaviours, health-related quality of life, and adverse events. An economic analysis will consider both within trial costs and a model extrapolating the results thereafter. A qualitative sub study will gain insights into the views, experiences and decision making processes of patients and health care professionals focusing on the acceptability of self-monitoring and telemonitoring in the routine management of hypertension.

**Discussion:**

The results of the trial will be directly applicable to primary care in the UK. If successful, self-monitoring of BP in people with hypertension would be applicable to hundreds of thousands of individuals in the UK.

**Trial registration:**

ISRCTN 83571366. Registered 17 July 2014

## Background

Blood pressure (BP) is a key risk factor for cardiovascular disease, the largest cause of morbidity and mortality worldwide [1, 2]. A 10 mmHg reduction in BP is estimated to lead to a 41% reduction in stroke and a 22% reduction in coronary heart disease [3]. National and international surveys suggest that, despite significant improvements in recent years, BP control within the population remains sub-optimal [4–7]. Self-monitoring as an intervention has been shown to reduce BP [8, 9], improve adherence to antihypertensive medication [10], and reduce primary care consultation rates at no additional cost [11]. Telemonitoring is associated with reduced BP but there are limited data relevant to a UK context, particularly with longer than 6 months follow-up [12, 13]. Furthermore, the evidence concerning the use of self-monitoring to guide GPs to titrate anti-hypertensives is equivocal with one systematic review finding the effect of self-monitoring on BP reduction becomes non-significant when a medication titration protocol is used [14].

The current (2004, updated 2006 & 2011) National Institute for Health and Care Excellence (NICE) guideline states: “the value of routinely using … home (BP) monitoring devices has not been established: their appropriate use in primary care remains an issue for further research” [15]. This trial aims to evaluate whether GP led antihypertensive titration using self-monitoring results in lower systolic BP (SBP) compared to usual care and whether telemonitoring reduces BP over and above self-monitoring alone.

## Methods and design

### Study aims, research questions and outcomes

The primary aim of TASMINH4 is to compare the management of hypertension in primary care using self-monitored BP to make treatment decisions, with or without telemonitoring, with usual care.

The trial has four main research questions:Does self-monitoring guided titration of antihypertensive medication, with or without telemonitoring, lead to better BP control in people with hypertension in primary care?Does self-monitoring guided titration of antihypertensive medication with telemonitoring lead to better BP control than self-monitoring guided titration using paper-based recording of BP?Is the management of hypertension through self-monitoring cost-effective?What are the views of patients and their clinicians regarding self-monitoring guided titration of antihypertensive medication, with or without telemonitoring?

The primary outcome of the trial will be the difference in SBP (mean of 2^nd^/3^rd^ readings, mmHg) at 12 month follow-up between intervention and control adjusted for baseline BP, gender, BP target, CVD history and practice.

Secondary outcomes (see Table 1, in each case also adjusted for baseline values and co-variates) will include:

**Table 1 Tab1:** Data collection throughout the trial

Baseline only:
1. Demographic questions: including age, race, marital status, occupation, and education
2. Duration of hypertension [from notes]
3. Past medical history [from notes and corroborated by patients]
4. Contraindications to anti-hypertensives
5. Short orientation memory test [22]
6. Height
Baseline and follow-up:
1. New medical history (in last 6/12 months)
2. Blood pressure (sitting plus standing)
3. Current anti-hypertensive medications including complementary herbal or dietary supplements for BP lowering
4. Weight and waist circumference
5. Symptoms part plus short form of Illness Perception Questionnaire [23]
6. Short-form of the State-Trait Anxiety Inventory [24]
7. EQ-5D 5L [25]
8. BP measurement preference [26] [Baseline and 12 m follow up only]
9. Medication Adherence Rating Scale (MARS) Questionnaire [27] [Baseline and 12 m follow up only]
10. Beliefs about Medicines Questionnaire [28] [Baseline and 12 m follow up only]
11. Stanford Expectations of Treatment Scale (SETS) Items 1–6 [29] [Baseline and 12 m follow up only]
12. Lifestyle questions: alcohol (Audit-C [30]), diet (Short Food Frequency Questionnaire [31]), exercise (Godin Leisure-Time Exercise Questionnaire [32]), smoking (Smoking tool kit [33]) [Baseline and 12 m follow up only]

Blood Pressure OutcomesDifference in SBP at 6 months follow up between intervention and controlDifference in diastolic BP at six and 12 months follow up between intervention and controlAll BP comparisons using mean of 2^nd^-6^th^ readings (BP-Tru automated blood pressure monitor, (BP TRU BPM 200; BP TRU Medical Devices, Coquitlam, BC, Canada) [16].

Tertiary Outcomes

Adverse eventsClinical Events: admissions, cardiovascular events, deathsAnxietySide effects of medication

Medication OutcomesMedication prescription: both number and defined daily doseAdherence to medicationBeliefs about medicines, expectations of treatment, illness perceptions

Fidelity to interventionGP fidelity to medication titration protocolPatient fidelity to monitoring regime

LifestyleAlcohol, diet, smoking, exercise

Quality of LifeEQ-5D-5L

Economic Outcomes:Resource use and costsWithin trial effectiveness will be assessed in terms of cost per 1 mmHg blood pressure reduction. Long term cost effectiveness will be assessed by linking differences in blood pressure observed in the trial to cardiovascular events with a lifetime horizon.

Qualitative Analysis:

The views of patients and clinicians will be assessed through depth interviews in the qualitative sub study (see below for further details).

### Study design and setting

TASMINH4 is a pragmatic unblinded individual patient randomised controlled trial with automated ascertainment of outcome and embedded economic and qualitative analyses.

### Study population

The study population will comprise people with poorly controlled hypertension managed in primary care. Eligibility criteria will be: age over 35 years, on the hypertension register, not already taking more than 3 anti-hypertensive agents, BP above 140/90 mmHg at the baseline clinic, and on a stable dose of current antihypertensive medication for at least 4 weeks prior to trial entry. Exclusion criteria will be orthostatic hypotension (20 mmHg or more systolic drop after standing for one minute, in order to avoid adverse events), BP not managed by their GP (limited possibility of antihypertensive titration), diagnosed atrial fibrillation (automated monitors not validated), unwilling to self-monitor, dementia or score over 10 on the short orientation memory concentration test (inability to undertake self-monitoring), female participant who is pregnant, lactating or planning pregnancy during the trial (management of essential hypertension in pregnancy is different), the partner or spouse of an individual already randomised in the trial (to avoid clustering within families), Chronic Kidney Disease (CKD) grade four or worse, any grade of CKD with proteinuria (both may have different BP targets), participants who have participated in another research trial involving antihypertensive medication in the past 4 weeks.

Potentially eligible patients will be identified from general practices via the UK Clinical Research Network (CRN). GP surgery staff supported by the research team/ CRN will conduct a practice-based computer search to identify patients that fulfil the eligibility criteria. GPs will be asked to check these computer generated lists and to remove people who are known to have terminal illnesses, those not managed by the GP and those thought to be unsuitable for the study in the opinion of the GP. The remainder will receive a postal invitation with a reminder after two weeks. Those wishing to decline participation may voluntarily return a form detailing basic demographic details as well as their reasons for declining.

### Baseline clinics

Patients will attend an initial baseline clinic where the study will be explained, informed consent gained, clinical measurements (height, weight, and BP) taken, demographics, past medical history, and key health behavioural and attitudinal related data collected (Table 1) by a trained researcher (either a research nurse, trained practice nurse, or member of the research team). Measurement of BP will use a validated automated electronic sphygmomanometer (BP TRU BPM 200). After five minutes of rest, six seated BP readings will be taken at 1-min intervals, of which the mean of the 2^nd^ and 3^rd^ reading will comprise the primary outcome. Randomisation will take place at the end of the baseline clinic.

### Randomisation

Patients will be randomised into one of three groups: self-monitoring alone, self-monitoring and telemonitoring, or usual care (1:1:1), using a fully-validated internet based randomisation system with manual telephone-based back up. Randomisation will be stratified by practice and minimisation, with a non-deterministic algorithm, will be used to ensure balance in baseline BP, gender and BP target (standard, older person or diabetic) across the groups.

### Intervention and control groups

***Usual care*** will consist of the participant’s BP being measured by their GP and/ or nurse at their practice, and adjustment of medication based on these measurements at the discretion of the health care professional.

The participants in the ***self-monitoring*** groups (self-monitoring alone and self-monitoring with telemonitoring) will be trained to monitor their BP using an automated electronic sphygmomanometer (Omron M10-IT) [17]. Patients will self-monitor BP daily for the first week of each month of the study. They will take their BP twice in the morning and evening (i.e. four times in all per day) [15]. Participant training will include instructions as to what to do in the presence of a high or low reading, using a guideline that contains simple colour-coded instructions. Very high or very low readings that persist when a third reading is taken five minutes after the second reading will trigger the patient to contact their practice for further advice.

### Medication reviews

All participants will be asked to book an appointment approximately one week later with the GP or practice nurse for a medication review. For the patients in the usual care arm, the GP will review the medication based on BP measurements taken in the clinic. The patients in the self-monitoring arms will monitor their BP for a week and bring the readings to their appointment. The GP will base the medication review on the readings done by the patient at home. After the medication review the GP/ nurse will register the patients in the telemonitoring arm on the text system and will train the patient in using the system.

### Communication of home readings

#### Self-monitoring group

Participants in the self-monitoring group will complete a simple two-part carbon copy form each month to record their daily BP readings, one copy to be kept by the patient, and one posted to the practice in a reply-paid envelope. The GP/ nurse will be asked to review these BP readings each month to determine whether a change in medication is required and the GP/ nurse will contact the patient if a medication change is required. At follow-up (6 and 12 months), data from participants’ BP machines will be uploaded and sent to the research team.

#### Telemonitoring group

Participants will be trained in the use of the telemonitoring equipment before commencing. Participants in the telemonitoring group will send their readings to a secure centralised database using a free SMS text message with web-based data entry back up. They will receive a reminder the day before their week of measurements, and two additional reminders in the week if no measurements are received by the system. Mean BP will be calculated automatically. High or low readings will trigger text alerts to the patient to contact their surgery for a BP check. The GP/ nurse will review the readings on a monthly basis via a web-based interface to determine whether a change in medication is required and the GP/nurse will contact the patient if a medication change is required. At follow-up (6 and 12 months), data from participants’ BP machines will be uploaded and sent to the research team.

### Target blood pressure

Target BP will be based on the NICE hypertension guideline with adjustment downwards by 5/5 mmHg for home as compared to office readings [18]. Thus people without diabetes under 80 years will have a home target of ≤135/85 mmHg; people over 80 years will have a home target of ≤145/85 mmHg; finally, people with diabetes will have a home target of ≤135/75 mmHg [15]. People requiring lower than standard targets will be excluded (hence the exclusions for CKD4 and proteinuria) (see Table 2).

**Table 2 Tab2:** Blood Pressure targets for the different groups for home readings and for readings taken in clinic

	BP target (mmHg)	BP target (mmHg)
Readings	Taken at home	Taken in clinic
<80 years	≤135/85	≤140/90
>80 years	≤145/85	≤150/90
Diabetic	≤135/75	≤140/80

### Follow-up

All patients will be asked to attend two follow-up clinics; 1 at 6 months and 1 at 12 months. Each clinic will be timetabled for no more than an hour, during which patients will have their BP and weight measured by the research team and will be asked to complete a questionnaire similar to the one completed at baseline. Participant flow through the trial is shown in Fig. 1. All data is collected on a case report form especially designed for the study.

**Fig. 1 Fig1:**
[figure not shown]
Flow through the trial

Patients who withdraw will not be replaced, but asked if they are prepared to attend follow-up clinics.

### Sample size considerations

The study requires a total sample of 1110 patients to be recruited with 370 patients in each arm. This is based on an assumption of a common standard deviation of 17 mmHg and a three way pairwise comparison. At least 367 participants per group (allowing for 15% attrition) would allow detection of a 5 mmHg difference between the groups (i.e. standardised effect size = 0.3) with 90% power and an adjusted alpha of 0.017 (2-sided) to account for all three pairwise comparisons. We estimate that around 120–150 practices will be required to recruit this size of sample, assuming an average list size of 7000, with a prevalence of hypertension of 13%, of whom 16% will respond to a trial invitation and 40% of these will be eligible. This corresponds to around 7–10 patients per practice of 7000 patients.

### Statistical analysis

Analysis will be on an intention-to-treat basis. A mixed model will analyse the primary outcome utilising data collected at 6 and 12 months from randomisation, adjusting for baseline BP measure and minimisation variables. An advantage of the mixed model is that it implicitly accounts for data missing at random. The model will include a random intercept for each participant to account for the repeated measures on the same participant. Time and randomised group will be fitted as fixed effects, with minimisation variables, region and history of CVD fitted as covariates. An interaction term between time and randomisation group will be included so that possible differences of treatment effect can be assessed at each time point. Similar methods will be used for other continuous outcomes. The two self-monitoring groups will first be compared to the usual care group. If both treatments are found to be more effective than usual care, they will be compared to each other.

Sensitivity analyses will be carried out to examine the robustness of the results with different assumptions about departures from randomisation policies and handling of missing data. A detailed statistical analysis plan will be prepared before any analyses are undertaken and before the trial database is locked.

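### The primary model fits region and leaves out practice, although randomisation is stratified by practice and the primary outcome is defined as practice-adjusted

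*Protocol article*

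**What the plan says.** Four places in the protocol article bear on this point.

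- **Randomisation.** "Randomisation will be stratified by practice and minimisation"; the minimisation "will be used to ensure balance in baseline BP, gender and BP target". Practice is the stratification factor and is listed apart from the three minimised variables.
- **Abstract, Methods/Design.** The primary outcome is the 12-month difference in clinic SBP "adjusted for baseline SBP, gender, BP target and practice".
- **Study aims, research questions and outcomes.** The same outcome is "adjusted for baseline BP, gender, BP target, CVD history and practice".
- **Statistical analysis.** The mixed model adjusts for baseline BP, and "Time and randomised group will be fitted as fixed effects, with minimisation variables, region and history of CVD fitted as covariates". A participant-level random intercept handles the repeated measures. Practice is not mentioned.

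Region is in neither outcome definition, is not a stated randomisation factor, and does not appear elsewhere in the article as shown.

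**The concern.** An analyst cannot satisfy the outcome definition and the model together: the first requires practice, and the second replaces it with region. This affects the estimate on which the trial will be judged. It also carries over to the other continuous outcomes, which are to be analysed by similar methods.

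There is a statistical side as well. Stratifying by practice makes the arms nearly balanced within each practice, so differences between practices largely cancel out of the treatment contrast. A model that ignores practice still counts that variance, in the participant intercept or the residual. Its standard error then describes a less precise design than the one used. Region can absorb differences between regions, but not those between practices in the same region.

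**Working it through.** **1. Adjustment sets side by side**

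| Term | Abstract | Outcome definition | Primary model |
|---|---|---|---|
| Baseline BP | yes (SBP) | yes | yes |
| Gender | yes | yes | yes (minimised) |
| BP target | yes | yes | yes (minimised) |
| CVD history | no | yes | yes |
| Practice | yes | yes | **no** |
| Region | no | no | **yes** |

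The material conflict is practice against region. The abstract's omission of CVD history is minor.

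**2. The plan's own sample size**

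Inputs from Sample size considerations: SD 17 mmHg, difference 5 mmHg, two-sided alpha 0.017, 90% power, 15% attrition.

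n = 2 × (17/5)² × (2.3867 + 1.2816)² = 23.12 × 13.456 = 311.1, so 312 evaluable per arm. Then 312/0.85 = 367.06, against 367 stated. The figure reproduces, and it makes no use of a practice effect.

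**3. Upper figure for the effect of omitting practice**

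Take a total SD of 17, 312 per arm and arms exactly balanced within practice.

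- Standard error reported without practice: 17 × √(2/312) = 1.361.
- True standard error: 1.361 × √(1 − ICC).
- Ratio: 1/√(1 − ICC).

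At ICC 0.10 the true standard error is 1.291 and the ratio 1.054. The effective critical value is 2.387 × 1.054 = 2.516, which gives an actual size of 0.0119. Power without practice is Φ(5/1.291 − 2.516) = Φ(1.356) = 91.3%. With practice it is Φ(3.872 − 2.387) = 93.1%.

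The article gives no ICC, so the range below is an assumption.

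| Assumed ICC | SE ratio | Actual alpha (nominal 0.017) | Power without practice | Power with practice |
|---|---|---|---|---|
| 0 | 1.000 | 0.0170 | 90.1% | 90.1% |
| 0.01 | 1.005 | 0.0165 | 90.2% | 90.4% |
| 0.02 | 1.010 | 0.0159 | 90.3% | 90.7% |
| 0.05 | 1.026 | 0.0143 | 90.7% | 91.7% |
| 0.10 | 1.054 | 0.0119 | 91.3% | 93.1% |

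**4. Allowing for imperfect balance**

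With 7–10 patients per practice over three arms, balance within practice is not exact. For a given allocation, the variance of the unadjusted difference is

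σ_b² Σ_k (n_1k/N_1 − n_0k/N_0)² + σ_w² (1/N_1 + 1/N_0),

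where σ_b² = 289 × ICC, σ_w² = 289 × (1 − ICC), n_1k and n_0k are the arm counts in practice k, and N_1 and N_0 are the arm totals.

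I averaged this over permuted blocks of three, with 1,110 patients in 120 to 150 practices and 15% lost at random. The ratio is about 1.01, 1.02 and 1.04 at ICC 0.02, 0.05 and 0.10. Separate simulations at ICC 0.10 gave 1.041 (130 practices of 7) and about 1.03 (with 15% attrition). At a ratio of 1.04 the actual size is about 0.013.

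These checks use one time point and simple blocks. They do not reproduce the two-visit model or the non-deterministic minimisation.

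**The case against.** The strongest reply is that this is a wording mismatch with a small cost in the safe direction. Much of that stands: the test would be slightly conservative, the estimate is not biased, and the planned power is met without practice in the model.

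Three further replies deserve an answer.

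- **The phrase for minimisation variables may have been meant to cover practice.** It is used loosely, since baseline BP is named beside it although it is itself minimised. But the Randomisation section lists practice separately, so the text does not support that reading.
- **The analysis plan will settle it.** Whether practice is fixed or random could be left there. But the article is not silent: it names its covariates and its random effect, and these conflict with its own outcome definition.
- **Region may stand in for practice.** It may absorb part of the between-practice variance, so the figures above could be too large. It cannot make the result practice-adjusted.

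A reader might infer that the standard errors will certainly be too wide. The documents do not support this: it requires a positive practice ICC after the other covariates, and none is given. A reader might also infer three rival adjustment sets of equal weight. The abstract's missing CVD history is ordinary condensation, and the outcome definition and the model agree on everything except practice and region.

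**Conclusion.** The contradiction is certain from the text: the primary model as written does not estimate the practice-adjusted difference that the article defines as its primary outcome. It should be corrected.

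The effect on precision is conditional and small. Over an assumed ICC of 0 to 0.10 the standard error is overstated by 0% to at most about 5%, with 3–4% more realistic at the top of that range. The gain from fitting practice is at most about 2 percentage points of power (93.1% against 91.3%). These figures rest on the assumed ICC range, the stated SD and attrition, and region absorbing nothing.

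Nothing here suggests an inflated false-positive rate or an underpowered trial. Patients, not practices, are randomised, so leaving out practice does not make the standard errors too small, as ignoring clusters would in a cluster-randomised trial.

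**What to change.** Add a random intercept for practice, with participants nested in practice, to the model in Statistical analysis. State one adjustment set in the abstract, the outcome definition and the analysis section: baseline SBP, gender, BP target and CVD history as fixed effects, and practice as a random effect. Drop region unless it is also added to the outcome definition. Apply the same set to the other continuous outcomes that use this model.

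The cost is a change of wording and one extra variance component to estimate. No new data and no change to the sample size are needed.

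### The telemonitoring versus self-monitoring comparison is charged for in a three-way alpha split and also gated on both arms beating usual care, so the 90% per-pair power does not describe the test as planned

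*Protocol article*

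**What the plan says.** Three parts of the protocol article bear on this.

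- **Sample size considerations.** The design basis is given as follows: "This is based on an assumption of a common standard deviation of 17 mmHg and a three way pairwise comparison". The number per arm is chosen to pick up 5 mmHg in any of these comparisons, and the error rates are set out in these words: "with 90% power and an adjusted alpha of 0.017 (2-sided) to account for all three pairwise comparisons". Read plainly, every pair is tested and every pair has 90% power.
- **Statistical analysis.** The two self-monitoring arms are each compared with usual care first. Then: "If both treatments are found to be more effective than usual care, they will be compared to each other". No alpha is given for either step, and no power is given for the sequence.
- **Study aims, research questions and outcomes.** The second of four main research questions asks whether titration guided by telemonitored readings will "lead to better BP control than self-monitoring guided titration using paper-based recording of BP". It is not made to depend on the answer to the first question.

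The abstract, background and discussion also present the added value of telemonitoring as an aim of the trial.

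**The concern.** The two sections describe different ways of handling multiplicity in the same family of three tests. Splitting alpha three ways pays in advance for testing all three pairs whatever the other results. A gate that opens only when both arms beat usual care is a hierarchical scheme, which would not normally need a share of alpha set aside for the last test. The third comparison bears both costs.

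At stake is a main research question. The gate is most likely to stay shut when telemonitoring works and paper-based self-monitoring does little, which is when the increment matters most. That case cannot be dismissed from the document itself, since the abstract and background describe the evidence for titration guided by self-monitoring as equivocal. If the conflict is left until results are known, the decision whether to make the comparison could be influenced by the data.

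**Working it through.** **Inputs from the sample size section:** difference 5 mmHg; common SD 17 mmHg; two-sided alpha 0.017; power 90%; attrition 15%; 370 recruited per arm.

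**1. Reproduce the stated number.** With z(1 − 0.017/2) = 2.387 and z(0.90) = 1.2816:

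n per arm = 2 × (2.387 + 1.2816)² × (17/5)² = 311.1, so 312 evaluable.

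312 / 0.85 = 367.06, against the stated 367. The per-pair figure reproduces.

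**2. Power of the third comparison if it is always tested.** Evaluable per arm = 370 × 0.85 = 314.5. The standard error of a difference is 17 × √(2/314.5) = 1.356 mmHg. For a true 5 mmHg difference, power = Φ(5/1.356 − 2.387) = Φ(1.30), about 90%.

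**3. Power with the gate.** Three independent arm means were simulated (SD 17, 314.5 per arm, millions of draws). A success requires self-monitoring to beat usual care, telemonitoring to beat usual care and telemonitoring to beat self-monitoring. Using 0.017 at each step is an assumption. The true telemonitoring advantage over self-monitoring is fixed at 5 mmHg. The self-monitoring effect against usual care is varied, because the document does not state one.

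| Self-monitoring / telemonitoring effect vs usual care (mmHg) | Gate opens | Gate opens and third test succeeds |
|---|---|---|
| 0 / 5 | 0.8% | 0.4% |
| 2.5 / 7.5 | 29% | 23% |
| 4 / 9 | 71% | 62% |
| 5 / 10 | 90% | 81% |
| 6 / 11 | 98% | 88% |
| 7 / 12 or more | over 99% | 90% |

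If both arms truly lower SBP by 5 mmHg, the gate opens in about 84% of trials, so the two arms are not formally compared in about 16%.

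**4. Effect of baseline adjustment.** The planned model adjusts for baseline BP, but the correlation between baseline and 12 months is not given. Taking residual SD = 17 × √(1 − r²) with assumed r:

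| Assumed r | Residual SD | 5 / 10 | 2.5 / 7.5 | 0 / 5 |
|---|---|---|---|---|
| 0.3 | 16.2 | 86% | 28% | 0.5% |
| 0.4 | 15.6 | 90% | 32% | 0.5% |
| 0.5 | 14.7 | 94% | 37% | 0.6% |

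**5. Is the gate needed for error control?** With no true differences, family-wise error is about 4.5% for three ungated tests at 0.017 and 3.2% with the gate. In any configuration the ungated bound is 3 × 0.017 = 0.051, which is 5% apart from the rounding of 0.05/3.

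**6. The alternative that keeps the order** (0.025 for each arm against usual care, then 0.05 for the third test if both reject). Family-wise error with no true differences is about 4.6%, and it is at most 5% when only the third null is true. The chance of reaching and winning the third test is about 88% at 5/10 mmHg and 0.9% at 0/5 mmHg.

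**The case against.** The case for leaving the text alone has several sound parts.

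- **The 90% is right as a per-pair figure.** A reader might infer that the sample size is wrong or that the trial is underpowered. The arithmetic does not support that, and the comparisons with usual care are unaffected. The abstract attaches the 90% to those comparisons. It is the wording in the sample size section, about the groups in general and all three pairs, that extends it to the third.
- **The shortfall depends on an effect the protocol never states.** It disappears at a self-monitoring effect of about 7 to 8 mmHg, and baseline adjustment can remove it at 5/10 mmHg. This stands. Adjustment does not rescue the 2.5/7.5 or 0/5 cases.
- **The gate has no stated alpha.** A reader might infer that a narrow miss at 0.017 in the self-monitoring arm forbids the comparison. The analysis section does not define what counts as being found more effective, and the analysis plan it promises may do so. Nor does it bar estimation: the model with a group-by-time interaction yields the contrast and its interval whichever tests are run.
- **Gating is a recognised choice.** It might be tempting to say that the gate protects nothing or makes the plan invalid. It lowers family-wise error from 4.5% to 3.2%. It is redundant for the 5% limit and conservative, but not invalid.

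The mismatch in the published text remains. A gate is stated, it conflicts with the basis of the sample size, and an analysis plan that follows it would inherit the conflict.

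**Conclusion.** The point holds as an inconsistency that should be fixed. The sample size section pays alpha for three unconditional comparisons, while the analysis section runs the third only conditionally, although it answers a main research question. The stated 90% does not describe that gated test. With SD 17, 0.017 at every step and a true 5 mmHg increment, the chance of reaching and winning it is about 81% when self-monitoring lowers SBP by the 5 mmHg design difference, 23% at 2.5 mmHg and 0.4% at no effect. The first figure may return to 90% or above with baseline adjustment; the other two remain low.

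The finding does not extend to an error in the sample size, inflation of type I error or any weakness in the comparisons with usual care. The size of the loss rests on the assumed self-monitoring effect and on the assumed alpha at the gate.

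**What to change.** Reconcile the two sections before database lock, in one of two ways.

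1. **Preferred:** delete the conditional sentence from the statistical analysis section, and state that all three 12-month pairwise contrasts are tested at 0.017 regardless of each other's results. This is the design that the sample size section assumes. It gives the third comparison its 90% power per pair and holds family-wise error at about 5%.
2. **If the order is to be kept:** drop the three-way split. Test each arm against usual care at 0.025, then telemonitoring against self-monitoring at 0.05 only if both reject. State that the power of the third comparison is conditional on the gate: about 88% at 5/10 mmHg and under 1% at 0/5 mmHg. This option does not help when only telemonitoring works.

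The cost is a sentence or two in the protocol and matching text in the analysis plan. No extra patients are needed under either option.
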